### Procedure for unblinding if needed {17b}

Not applicable.

## Data collection and management

### Plans for assessment and collection of outcomes {18a}

Data acquisition will be carried out using an eCRF, which is to be completed by the emergency care team following the resuscitation. The data collected will be supplemented with the ventilation parameters recorded by the emergency ventilators. The variables collected in the eCRF are shown in Table 1.

**Table 1 Tab1:** Variables collected in the eCRF

Category	Collected variables
Patient factors	Age (years), Sex, Comorbidities
Airway factors	Bag-mask ventilation before airway device placement (yes/no), Intubation (extraglottic airway device vs. endotracheal tube), Type of extraglottic airway device, Number of insertion attempts, Complications during insertion, Number of intubation attempts, Complications during intubation, Abandonment of intubation attempts, Re-intubation by emergency physician
Resuscitation data	Observed cardiac arrest (yes/no), Cardiac arrest observed by (layperson/emergency services), Layperson CPR performed (yes/no), Time to initiation of chest compressions, Resuscitation duration (minutes), Initial ECG findings, Defibrillation (yes/no), Number of defibrillations, Type of chest compressions (manual vs. mechanical), Type of mechanical compression device, Administration and cumulative dose of epinephrine and amiodarone
Intra-arrest ventilation data	Ventilation parameters set by emergency services (Pmax, PEEP, respiratory rate, tidal volume, inspiration-expiration ratio, FiO_2_, Ventilation mode: IPPV, BILevel, CCSV, Other), Ventilation parameters measured by Medumat Transport, Changes in ventilation parameters during resuscitation
Post-arrest treatment	Re-intubation from extraglottic airway to endotracheal tube (yes/no), Number of intubation attempts, Type and dose of analgesic, hypnotic, muscle relaxant, Complications in pre-hospital post-arrest phase (aspiration, ventilation issues, hypotension, re-arrest), Administration of catecholamines, Post-arrest ventilation settings
Additional outcome data	Consciousness at handover, ECG findings at handover, Glasgow Coma Scale, Vital parameters at handover (systolic blood pressure, heart rate, oxygen saturation, respiratory rate, etCO_2_), Initial blood gas analysis, Date of death, Hospital discharge date

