### Participant timeline {13}

#### Enrolment

*Time Point*: Patients will be enrolled *at the time of OHCA *(Fig. 1).*Inclusion Process*: Once a patient meets the inclusion criteria (OHCA, age ≥ 18 years, and undergoing mechanical ventilation), they will be immediately enrolled by the EMS team. The need for informed consent was waived by the responsible ethical committee.

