### Sample size {14}

The planned sample size is approximately 600 out-of-hospital cardiac arrest (OHCA) cases, with about 300 patients per group (PEEP vs. ZEEP).

The PerAVent trial is designed as a pilot and feasibility study, primarily aimed at evaluating the practical implementation of PEEP versus ZEEP ventilation in the pre-hospital setting and generating preliminary data for future confirmatory research.

The study hypothesis is that ventilation with PEEP (5 mbar) increases the probability of return of spontaneous circulation (ROSC) compared with ZEEP (0 mbar).

As this is a pilot study, no formal sample size calculation or power analysis has been performed, since no reliable prior data exist on which to base such assumptions. The chosen sample size is therefore based on feasibility considerations and expected case numbers within the participating emergency medical service regions over the planned study period.

The collected data will serve to estimate key parameters—such as recruitment rates, adherence, and effect size estimates—that may inform the design of a future confirmatory trial.

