### Recruitment {15}

Recruitment will occur across multiple EMS regions, including Gütersloh, Minden-Lübbecke, and Osnabrück. All eligible OHCA patients treated by EMS teams in these regions during the 12-month data collection period will be enrolled. The large geographic area and population served by these EMS units are expected to provide sufficient participant numbers.

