## Assignment of interventions: blinding

### Who will be blinded {17a}

In this study, the EMS personnel delivering the interventions (PEEP or ZEEP) will not be blinded, as they need to know which ventilation strategy to apply during resuscitation. Since the patients enrolled in the study are unaware of which group they are assigned to during the resuscitation, they are considered blinded.

However, the outcome assessors and data analysts who evaluate the results, including ROSC probabilities and other clinical outcomes, will be blinded to the group assignments to minimize bias in data interpretation and analysis.

This blinding ensures that the analysis is conducted without any knowledge of which intervention was applied, maintaining objectivity in assessing the study’s outcomes.

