### Data management {19}

Data from the study will be entered and managed using a centralized eCRF provided by the study center of the University of Bonn, which allows access to a for all study participants. All patient data will be recorded both in the eCRF and as part of the standard EMS documentation process.

To ensure data quality, several measures will be implemented. Data will be systematically coded to ensure consistency across all entries, with patient identifiers anonymized to protect confidentiality. All data entered into the app will be encrypted and securely stored in a centralized database, accessible only to authorized study personnel.

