### Methods in analysis to handle protocol non-adherence and any statistical methods to handle missing data {20c}

Missing or incomplete data will be monitored continuously through automated completeness checks within the eCRF. In cases of protocol non-adherence or deviations in data entry, the coordinating center will contact the respective EMS team for clarification and data verification.

All missing data and deviations from the protocol will be documented and reported transparently.

For the statistical analysis, missing data will be handled using appropriate methods depending on the type and extent of missingness. If feasible, multiple imputation will be applied for missing covariate data. Sensitivity analyses will be conducted to evaluate the robustness of the primary results under different assumptions regarding missingness and protocol adherence.

This approach ensures transparency, minimizes potential bias, and maintains the methodological rigor of the study despite the operational challenges of data collection in the pre-hospital setting.

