This study faces several practical and operational challenges related to its conduct in a pre-hospital emergency setting. One key issue is the logistics of enrolling patients during OHCA, where time-sensitive decisions must be made. Ensuring that EMS personnel adhere to the study protocol while delivering urgent care will require thorough training and clear communication. Another challenge is the cluster-randomized design, which involves different EMS regions rotating between the PEEP and ZEEP groups. This design requires careful coordination and monitoring to ensure that randomization is properly implemented and that no unintentional crossover occurs between groups. To ensure this, it is planned to program the emergency ventilation modes of the ventilators according to cluster randomization. In addition, regular training sessions and stickers placed on the ventilators are intended to make rescue service staff aware of which group the patient is in at the time of resuscitation.

Additionally, data collection during such high-pressure, fast-paced environments may be difficult. Ensuring accurate and complete documentation of ventilation settings and patient outcomes will be critical. For this reason, it is planned to document the measures taken following the operation using an application-based eCRF. In addition, the emergency respirators will be read out after use so that real-life data on the ventilation settings measured by the respirators is available.

Moreover, variability in care practices across EMS regions may introduce confounding factors that will need to be accounted for in the statistical analysis.

However, the treatment of resuscitation is highly standardized by the regularly updated resuscitation guidelines and the rescue service staff in Germany are regularly re-certified in the performance of CPR in accordance with their legally prescribed further training obligation.

These issues, along with the ethical considerations of conducting research in life-threatening situations, will need careful attention throughout the study.

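### No stated check would detect an eligible ventilated arrest for which the unblinded crew opened no eCRF, so the protocol should state that EMS records and ventilator read-outs are matched to eCRF entries

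*Protocol article*

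**What the plan says.** **Enrolment.** Recruitment {15} intends full capture: "All eligible OHCA patients treated by EMS teams in these regions during the 12-month data collection period will be enrolled". Under Enrolment, once a patient meets the criteria, "they will be immediately enrolled by the EMS team". Consent is waived and the arm follows from region and calendar period, so neither consent nor individual randomisation leaves a record of the case.

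**Data capture.** Plans for assessment and collection of outcomes {18a} states: "Data acquisition will be carried out using an eCRF, which is to be completed by the emergency care team following the resuscitation". Ventilator recordings are described there as a supplement to those data.

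**Blinding.** Who will be blinded {17a} states that "the EMS personnel delivering the interventions (PEEP or ZEEP) will not be blinded". The Discussion adds that training and stickers on the ventilators tell staff the current arm.

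**Completeness.** The section on non-adherence and missing data {20c} states: "Missing or incomplete data will be monitored continuously through automated completeness checks within the eCRF". The coordinating centre queries crews about non-adherence and data-entry deviations.

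**Other records.** Data management {19} states: "All patient data will be recorded both in the eCRF and as part of the standard EMS documentation process". The Discussion adds that "the emergency respirators will be read out after use so that real-life data on the ventilation settings measured by the respirators is available".

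**Purpose.** Sample size {14} states: "The collected data will serve to estimate key parameters—such as recruitment rates, adherence, and effect size estimates". Additional statistical considerations calls for intention-to-treat analysis throughout.

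**The concern.** An automated completeness check acts on a record that exists. It can find an empty field, but not an absent case. Here the form is completed after the event, by people who know the arm and the result. A crew that is tired, busy or discouraged after a failed resuscitation may be less likely to open one. No conscious favouritism is needed.

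Three things depend on complete capture:

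- the intention-to-treat claim, which otherwise covers reported cases and not treated ones;
- the ROSC proportions and recruitment rate that the pilot is to hand to a confirmatory trial;
- the PEEP versus ZEEP comparison, if outcome-dependent omission differs between arms.

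Drift over time could produce the third without any preference for an arm. Three regions cannot divide evenly between the two treatment orders. If reporting of failed resuscitations waned in the second half-year, the effect need not cancel between arms.

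**Working it through.** **Step 1. Is there a stated check that finds a missing case?** The candidate sections, side by side:

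| Section | What it does | Finds an unopened form? |
|---|---|---|
| Missing data {20c} | Completeness checks within the eCRF; queries on data entry | No |
| Adherence {11c} | Periodic review of recorded data for deviations | Not stated |
| Outcome collection {18a}; Discussion | Ventilator data supplement the eCRF; devices read out | Could, but no matching stated |
| Data management {19} | Parallel standard EMS documentation | Could, but no matching stated |
| Retention {18b}; Auditing {23} | Not applicable | No |
| Oversight {5d} | Adjudication committee and data management team | Not described as case-finding |

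**Step 2. Would the planned total reveal a loss?** The article makes no power calculation, so its figure of about 600 cases (about 300 per arm) cannot be reproduced, only checked for plausibility. Inputs are 650,000 inhabitants (Study setting) and 67 to 170 arrests per 100,000 per year (Background).

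- 650,000 × 67/100,000 = 435.5
- 650,000 × 170/100,000 = 1,105
- 600/650,000 = 92.3 per 100,000

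The planned number is plausible, but a range of about 436 to 1,105, before any eligibility criterion is applied, is too wide to expose missing cases.

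**Step 3. Size of bias, all reporting rates assumed.** Let p be the true ROSC proportion, and a and b the form-completion rates for ROSC and non-ROSC cases.

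Observed ROSC = pa / [pa + (1 − p)b]

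Spurious OR with no true effect = (a/b in PEEP) / (a/b in ZEEP)

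With p = 0.40 (assumed):

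- PEEP, a = 0.95, b = 0.80: 0.38/(0.38 + 0.48) = 44.2%
- ZEEP, a = b = 0.875: 0.35/(0.35 + 0.525) = 40.0%
- Spurious OR = (0.95/0.80)/1 = 1.19
- PEEP with b = 0.70 instead: 0.38/(0.38 + 0.42) = 47.5%

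In the first scenario the overall share captured is 0.38 + 0.48 = 86.0% in PEEP and 87.5% in ZEEP. That is 258 and 262.5 of 300, so case counts by arm would look balanced.

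**Step 4. One-arm omission across a range.** Suppose a share u of non-ROSC cases goes unreported in the PEEP arm only, with 300 eligible per arm. The Background gives usual ROSC of at most 30%, and about 50% in one cited study. The last two columns give Φ(difference/SE − 1.96), the chance of a spurious two-sided 5% result favouring PEEP. They ignore clustering; the nominal value is 2.5%.

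| u | Observed PEEP ROSC, p = 30% | p = 50% | Spurious OR, 1/(1 − u) | Chance, p = 30% | p = 50% |
|---|---|---|---|---|---|
| 5% | 31.1% | 51.3% | 1.05 | 5% | 5% |
| 10% | 32.3% | 52.6% | 1.11 | 9% | 9% |
| 20% | 34.9% | 55.6% | 1.25 | 23% | 26% |
| 30% | 38.0% | 58.8% | 1.43 | 49% | 55% |

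**Step 5. Equal omission.** If the same share of non-ROSC cases is lost in both arms, the OR is 1. The proportions are still wrong: a true 30% appears as 32.3% (u = 10%) or 34.9% (u = 20%) in both arms.

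**The case against.** The strongest reply is that this is a condensed article. Matching case lists is operational detail that often sits in a monitoring or data-management plan, and the article refers elsewhere to governance documents and operating procedures not shown. Nothing in the two key sections is false, and they do not contradict each other. Part of this stands: an unseen document may already contain the step. But the article is not silent on completeness. It names its method, and that method cannot verify the full enrolment it promises.

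Several stronger readings are tempting and are not supported:

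- *The form is the only way into the trial.* The article says who completes it, not that no other route exists, and it describes enrolment as immediate.
- *Unreported cases are invisible, and the other records are not used to find them.* EMS documentation and ventilator read-outs exist and could reveal such cases. The article does not say whether they are matched.
- *The recruitment rate has no denominator.* EMS records could supply one.
- *The PEEP effect is biased.* Nothing shows that reporting differs by arm. The same regional services report under both arms, which makes a marked arm-specific pattern less obvious, and equal omission leaves the OR at 1.

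The trial also calls itself a pilot not meant to establish superiority. That lowers the stakes for the effect estimate, but not for the recruitment rate and ROSC proportions, which are its stated products.

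**Conclusion.** The gap is real and worth closing. As the article stands, no stated check would detect an eligible ventilated arrest without a form, and the form is completed by an unblinded crew after the outcome is known. Outcome-dependent omission would distort the ROSC proportions. Any omission would understate recruitment. The PEEP effect is biased only if the dependence on outcome also differs by arm or half-year, which is a risk and not something the article shows.

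The size is hypothetical throughout. Under the assumed rates, spurious differences run from about 4 points (44.2% against 40.0%) to 7.5 points (47.5% against 40.0%). Loss of 10 to 20% of non-ROSC cases in one arm alone gives an OR of 1.11 to 1.25. With equal omission the OR is 1.

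**What to change.** In Plans for assessment and collection of outcomes {18a} and the missing-data section {20c}, state that:

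1. for each region and period, standard EMS records and ventilator read-outs are matched to eCRF entries;
2. any eligible ventilated arrest without a form is queried and included in the intention-to-treat population. Its arm follows from region and date, and its ROSC status is taken from the EMS record, noting that the same unblinded crew may have written that record;
3. the share captured is reported by arm and region-period. Because overall shares can look balanced (86.0% against 87.5% above), it should also be split by recorded ROSC status.

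The cost is periodic list matching by the coordinating centre and a linkage key, which must be kept although identifiers are anonymised at data entry (Data management {19}, Confidentiality {27}). The key should be secured before the final analysis. No new measurement or patient contact is needed. If an existing plan already contains this step, a sentence citing it is enough.

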### Plans to promote participant retention and complete follow-up {18b}

Not applicable.

### Data management {19}

Data from the study will be entered and managed using a centralized eCRF provided by the study center of the University of Bonn, which allows access to a for all study participants. All patient data will be recorded both in the eCRF and as part of the standard EMS documentation process.

To ensure data quality, several measures will be implemented. Data will be systematically coded to ensure consistency across all entries, with patient identifiers anonymized to protect confidentiality. All data entered into the app will be encrypted and securely stored in a centralized database, accessible only to authorized study personnel.

### Confidentiality {27}

Personal information about potential and enrolled participants will be handled with strict confidentiality at all stages of the trial. The following measures will be taken to ensure data protection. Participant data, including personal identifiers, will be collected via secure electronic systems, such as the eCRF provided by the University of Bonn. During data entry, personal identifiers will be anonymized, and participants will be assigned unique study IDs to ensure confidentiality. Access to identifiable information will be limited to authorized personnel only. Study data shared with external parties or for analysis purposes will be fully de-identified, ensuring no participant can be traced back using the shared information. All data will be stored on secure, encrypted servers, both during the trial and after its completion. Physical copies of documents, if needed, will be kept in locked, access-controlled storage. Data will be retained according to regulatory requirements and then properly disposed of to ensure no breach of confidentiality. Additionally, participants are subject to the legal data protection regulations.

### Plans for collection, laboratory evaluation and storage of biological specimens for genetic or molecular analysis in this trial/future use {33}

Not applicable.

## Statistical methods

### Statistical methods for primary and secondary outcomes {20a}

For the primary outcome (ROSC), a mixed logistic regression model will be used to analyze the difference in the probability of achieving ROSC between the two groups (PEEP vs. ZEEP). This model will account for the cluster-randomized design, adjusting for potential correlations within clusters (EMS regions).

For secondary outcomes, such as re-arrest rate, death during pre-hospital care, hospital admission during ongoing resuscitation, hospital admission with spontaneous circulation, SpO₂, FiO₂, and etCO₂ at hospital admission, linear regression models will be used for continuous variables, while logistic regression will be applied for binary outcomes (e.g., shockable vs. non-shockable rhythms).

The models will include relevant covariates, such as age, comorbidities, and other baseline characteristics, to adjust for potential confounders. Random effects will be included to account for variability between EMS regions.

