### Trial design {8}

The study is designed as a prospective, cluster-randomized, multicenter interventional pilot trial. It employs a cluster-randomized design, where each participating EMS region in pre-defined time frames represents a cluster. The clusters will be randomly allocated to either the intervention group (receiving a PEEP of 5 mbar) or the control group (receiving ZEEP or 0 mbar) for a defined period of 6 months, followed by a crossover, where the same regions will switch to the opposite treatment arm for another 6 months.

The allocation ratio is 1:1 within each cluster, meaning that each group (intervention and control) will receive an equal number of patients. Since this is a pilot study, it is designed primarily to assess the feasibility and preliminary effects of the intervention rather than to definitively establish superiority. The results will provide the groundwork for future, more extensive studies.

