#### Interventions

PEEP or ZEEP Intervention:o*Time Point*: Immediately after advanced airway management is secured (using either an extraglottic airway device [EAD] or an endotracheal tube [ETT]).oThe assignment to PEEP or ZEEP is predetermined, as the defined time period dictates whether the patient will receive PEEP (5 mbar) or ZEEP (0 mbar). The sequence of these time periods has been randomized via cluster randomization.oThe intervention will continue throughout the resuscitation efforts until ROSC or cessation of resuscitation efforts.

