## Assignment of interventions: allocation

### Sequence generation {16a}

In this study, the allocation sequence will be generated using *cluster randomization*. Each participating EMS region (Gütersloh, Minden-Luebbecke, and Osnabrueck) will represent a cluster. The clusters will be randomized to either the intervention group (PEEP) or the control group (ZEEP) using *predefined randomization blocks*, which are based on 6-month intervals. After 6 months, the clusters will switch to the opposite group, ensuring that each region experiences both interventions.

To reduce predictability and maintain the integrity of the randomization, the allocation sequence and any randomization restrictions, such as block sizes, will be managed centrally and will not be accessible to the EMS personnel enrolling participants or assigning interventions. This ensures that the allocation remains concealed until implementation.

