## Trial status

This is the second version of the protocol. Recruitment commenced on June 1, 2025, and is expected to be completed by May 31, 2026. The study is currently ongoing across the participating emergency medical service (EMS) regions.

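### The primary ROSC model adjusts for EMS region but names no period term, although three regions crossing over once leave treatment correlated with half-year

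*Protocol article*

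**What the plan says.** **Design.** Trial design {8} has regions allocated to one arm for 6 months, "followed by a crossover, where the same regions will switch to the opposite treatment arm for another 6 months". Sequence generation {16a} makes each of the three EMS regions a cluster and adds: "After 6 months, the clusters will switch to the opposite group, ensuring that each region experiences both interventions". The Interventions part of the participant timeline says that the calendar period determines which setting a patient receives, and that "The sequence of these time periods has been randomized via cluster randomization". Trial status gives the window: "Recruitment commenced on June 1, 2025, and is expected to be completed by May 31, 2026". If the switch falls at 6 months, the periods are June to November 2025 and December 2025 to May 2026.

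**Analysis.** Statistical methods {20a} says that "a mixed logistic regression model will be used to analyze the difference in the probability of achieving ROSC between the two groups". It states how the design is handled: "This model will account for the cluster-randomized design, adjusting for potential correlations within clusters (EMS regions". It continues: "The models will include relevant covariates, such as age, comorbidities, and other baseline characteristics, to adjust for potential confounders", and "Random effects will be included to account for variability between EMS regions". The article names neither period, calendar time, season nor sequence as a model term.

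**The concern.** The analysis structure described in {20a} fits a parallel cluster trial, where the main design feature to respect is that patients in one region resemble each other. This trial is a two-period cluster crossover. Within a region, PEEP and ZEEP patients are always treated in different half-years. A region effect removes differences between regions; it cannot remove a change over time that all regions share.

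Such a change would cancel if half the patients came from regions that start with PEEP and half from regions that start with ZEEP. With three regions this generally fails. Part of any difference between the half-years, for example in case mix, response times or growing familiarity with the trial procedures, is then credited to or held against PEEP. The direction depends on which order has the majority and which half-year has the higher ROSC proportion. At stake are the primary estimate and, if the same terms are used, every secondary one.

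**Working it through.** The article states no alpha, power or target effect (Sample size {14}), so there is no figure to reproduce. The check asks how much of a common period effect reaches the PEEP estimate.

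**Inputs from the article**
- 3 regions, two 6-month periods, one switch (Trial design {8}, Sequence generation {16a}).
- About 600 patients, about 300 per arm (Sample size {14}). With equal regions and equal halves: 600 / 6 = 100 per region-period.
- Usual ROSC of at most 30% (Background and rationale); 30% is used.

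**Assumptions, not in the article**
- Equal recruitment in both half-years.
- Period odds ratios of 1.1, 1.25 and 1.5.
- Nominal two-sided 5% test.
- Region shares equal, or 45/35/20%.

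**Step 1: share of the period effect that becomes bias**

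Bias ≈ (share of patients in PEEP-first regions − share in ZEEP-first regions) × period difference. In size, with one region of share *s* alone in its order, the factor is |1 − 2*s*|.

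| Allocation | Factor |
|---|---|
| Equal regions, 2:1 | 1 − 2/3 = 1/3 |
| 45/35/20%, the 45% region alone | 1 − 0.90 = 0.10 |
| 45/35/20%, the 35% region alone | 1 − 0.70 = 0.30 |
| 45/35/20%, the 20% region alone | 1 − 0.40 = 0.60 |
| All regions in one order (3:0) | 1 |

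The factor is zero only if one region recruits as many patients as the other two together and is alone in its order.

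**Step 2: false positives with no true PEEP effect (equal regions, 2:1, no period term)**

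SE of the log odds ratio ≈ √(2 / (300 × 0.3 × 0.7)) = √(2/63) = 0.178.

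| Period OR | Bias = ln(OR)/3 | Bias / SE | False positives |
|---|---|---|---|
| 1.1 | 0.032 | 0.18 | about 5.4% |
| 1.25 | 0.074 | 0.42 | about 7.0% |
| 1.5 | 0.135 | 0.76 | about 11.8% |

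The last column is Φ(−1.96 + Bias/SE) + Φ(−1.96 − Bias/SE). Simulation of 40,000 trials per setting gave 7.1% and 11.9% for odds ratios of 1.25 and 1.5 without the period term, and 4.9% to 5.1% with it.

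**Step 3: cost of adding the period term**

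After region is removed, the correlation of treatment with period equals the factor in Step 1. The variance of the PEEP effect is multiplied by 1/(1 − factor²).
- Equal regions, 2:1: 1/(1 − 1/9) = 1.125; √1.125 = 1.06, so the interval is about 6% wider.
- 45/35/20% with the smallest region alone: 1/(1 − 0.36) = 1.56; √1.56 = 1.25, so 25% wider.
- 3:0: treatment and period are identical and the term cannot be estimated.

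**Step 4: when the trade pays (equal regions, 2:1)**

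Mean squared error breaks even when bias² = 0.125 × 0.178², that is, bias = 0.063. The period log odds ratio is then 3 × 0.063 = 0.189, an odds ratio of about 1.2. Below that, omitting the term gives a slightly smaller mean squared error; above it, including the term does.

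**The case against.** **The article is a summary.** The covariate list is open, the exact fixed terms are usually left to the SAP, and nothing in {20a} excludes period. That is fair, and a SAP may already contain the term. But {20a} does more than stay silent: it says by what means the design is accounted for, and names region. Period is a design factor, not a patient baseline characteristic, so the open list does not naturally cover it.

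**The cluster may be the region-period.** Trial design {8} describes a cluster as a region within a set time frame, whereas {16a} and {20a} name the region. A region-period random effect would carry some period variation into the standard error, so the false-positive rates above would not apply as they stand. It still would not remove a shift common to all regions.

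**The trial is a pilot.** No alpha is set and the article disclaims a definitive test of superiority. This stands and limits the severity. The false-positive rates are a yardstick for the bias, not error rates that the protocol promised to control.

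**The period effects are assumed.** This also stands. The article gives no seasonal ROSC figure, and near an odds ratio of 1.1 the omission hardly matters.

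**Stronger readings that the article does not support.** A reader might infer that PEEP is wholly confounded with season. That needs all three regions to share one order. Independent randomisation would give this with probability 2/8, but {16a} mentions centrally managed blocks and possible restrictions, and the realised order is not given; the article neither states nor excludes it. A reader might also infer that a period term guarantees a 5% error rate. That holds only without extra variation between region-periods. With an assumed region-period SD of 0.1 or 0.2 on the logit scale, the error is about 7.5% or 15% even with the term.

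**Conclusion.** The point holds as a should-fix. The design handling written in {20a} does not match the crossover described in {8}, the participant timeline and {16a}. Followed as written, it passes part of any common half-year difference in ROSC into the PEEP estimate. With equal regions at 2:1 that part is one third. Its practical size ranges from negligible to a false-positive rate of about 12% over the assumed period odds ratios of 1.1 to 1.5. With unequal regions the part depends on which region is alone in its order.

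The conclusion that bias is possible rests only on the number of regions and the single switch. Its size rests on the assumed period effect, region shares, 30% ROSC and equal recruitment in the two halves. The pilot status lowers the stakes without removing them: Sample size {14} says effect estimates may inform a later confirmatory trial, and a contaminated estimate would carry over into that design.

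**What to change.** In {20a}, and in the SAP if it does not already say so:

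- Add a fixed effect for period (half-year 1 or 2) to the primary model and to all secondary models, alongside treatment, the patient covariates and the planned random effect for region. Replacing the region random effect by fixed effects is not needed for this point.
- Report the realised order of each region.
- State in advance that, if all three regions had the same order, the PEEP effect cannot be separated from calendar period.

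**Cost.** Wording only: the calendar period already determines each patient's treatment, so no new data are needed. No interim analysis is planned, so the change can be made before outcomes are analysed. The statistical price is the variance factor shown above: 1.125 with equal regions at 2:1, and up to 1.56 with shares of 45/35/20%. If the true period effect is small, this is paid for little gain. The term does not remove changes over time that differ between regions; with three regions those remain a limitation to be acknowledged in the report.
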